# Protocol for a Randomised controlled trial to Evaluate the effectiveness and cost benefit of prescribing high dose FLuoride toothpaste in preventing and treating dEntal Caries in high-risk older adulTs (reflect trial)

**DOI:** 10.1186/s12903-019-0749-x

**Published:** 2019-05-24

**Keywords:** Caries, High-concentration, Fluoride, Toothpaste, Older, Adults, General dental practice

## Abstract

**Background:**

Dental caries in the expanding elderly, predominantly-dentate population is an emerging public health concern. Elderly individuals with heavily restored dentitions represent a clinical challenge and significant financial burden for healthcare systems, especially when their physical and cognitive abilities are in decline. Prescription of higher concentration fluoride toothpaste to prevent caries in older populations is expanding in the UK, significantly increasing costs for the National Health Services (NHS) but the effectiveness and cost benefit of this intervention are uncertain. The Reflect trial will evaluate the effectiveness and cost benefit of General Dental Practitioner (GDP) prescribing of 5000 ppm fluoride toothpaste and usual care compared to usual care alone in individuals 50 years and over with high-risk of caries.

**Methods/design:**

A pragmatic, open-label, randomised controlled trial involving adults aged 50 years and above attending NHS dental practices identified by their dentist as having high risk of dental caries. Participants will be randomised to prescription of 5000 ppm fluoride toothpaste (frequency, amount and duration decided by GDP) and usual care only. 1200 participants will be recruited from approximately 60 dental practices in England, Scotland and Northern Ireland and followed up for 3 years. The primary outcome will be the proportion of participants receiving any dental treatment due to caries. Secondary outcomes will include coronal and root caries increments measured by independent, blinded examiners, patient reported quality of life measures, and economic outcomes; NHS and patient perspective costs, willingness to pay, net benefit (analysed over the trial follow-up period and modelled lifetime horizon). A parallel qualitative study will investigate GDPs’ practises of and beliefs about prescribing the toothpaste and patients’ beliefs and experiences of the toothpaste and perceived impacts on their oral health-related behaviours.

**Discussion:**

The Reflect trial will provide valuable information to patients, policy makers and clinicians on the costs and benefits of an expensive, but evidence-deficient caries prevention intervention delivered to older adults in general dental practice.

**Trial registration:**

ISRCTN: 2017-002402-13 registered 02/06/2017, first participant recruited 03/05/2018.

Ethics Reference No: 17/NE/0329/233335.

Funding Body: Health Technology Assessment funding stream of National Institute for Health Research.

Funder number: HTA project 16/23/01.

Trial Sponsor: Manchester University NHS Foundation Trust, [name].

The Trial was prospectively registered.

**Electronic supplementary material:**

The online version of this article (10.1186/s12903-019-0749-x) contains supplementary material, which is available to authorized users.

## Background

The UK has an ageing population. The number of people of State Pension Age and over is projected to increase by 32.7% from 12.4 million in mid-2014, to 16.5 million by mid-2039. Likewise the number of people aged 75 and over is projected to rise by 89.3%, to 9.9 million, over the same period [1]. Whilst an increase in life expectancy should be celebrated, attention needs to be given to the complex health needs, including oral health needs, of the growing population of older people.

Dental caries is preventable, yet it is the most common disease worldwide. In high-risk older populations it is an important public health issue, as the number of older people who retain their natural teeth is growing rapidly. In England in 2009, 6% of the adult population were edentulous, compared to 28% in 1978 [2]. Dentate older adults tend to have extensively restored teeth [2], mainly due to them having grown-up prior to the widespread use of fluoride toothpaste (introduced in the 1970’s). For these older adults, the risk of developing dental caries increases due to the presence of restorations and prostheses (bridges or dentures) that increase plaque retention, dry mouth (often as a result of polypharmacy), exposed root surfaces and a cariogenic diet. The oral health of these individuals will decline as their physical and cognitive abilities deteriorate, resulting in a growing population health problem with significant financial repercussions for the NHS; so prevention of caries is important [3].

Recent National Institute for Health and Care Excellence (NICE) guidance recognised the impact poor oral health can have on older individuals’ ability to eat, speak and socialize [4]. This guidance focused on those living in care homes (either nursing or residential), however, the majority of the 11 million adults in the UK, aged 65 years or over, live in their own homes, with less than 4% (approximately 414,000) living in some form of care home [4]. It is therefore important to establish a strong evidence base for the management of the oral health needs of older people across all residential settings. In the four countries of the UK dental policy on reforming NHS dental contracts places an emphasis on General Dental Practitioners (GDPs) providing effective caries prevention [5] and they have a central role in maintaining the oral health of the older population. The significant reductions in dental caries prevalence and severity over the last 40 years have primarily been attributed to fluoride toothpaste [6]. More recently high concentration, prescription-only fluoride toothpaste has been used increasingly in the management of patients with high risk of caries [7].

The current evidence to support prescription of high concentration fluoride toothpaste (specifically 5000 ppm (ppm) toothpaste) to prevent caries is weak [8–10]. A Cochrane review of different doses of fluoride toothpaste did not include any randomised controlled trials of 5000 ppm fluoride, however the review did find a dose-response relationship between the concentration of fluoride in toothpaste and caries prevention, with greater caries prevention for higher doses of fluoride [10]. This review is currently being updated to include adults: no trials on the prevention of coronal caries through the use of 5000 ppm toothpaste have been identified. A more recent review of high fluoride concentration toothpastes included four studies (randomised and non-randomised) with 5000 ppm fluoride toothpaste [11]. None of these studies meet the inclusion criteria for the Cochrane review and all have significant design and methodological limitations. However, despite the weak evidence base, GDPs in England are advised by national guidance published by Public Health England to prescribe high concentration 2800/5000 ppm fluoride toothpaste for older adults with active caries or those at risk of developing caries [12]. The prescription of this technology is expanding; in England in 2014 1.3 million items were prescribed at a cost of £17 million [13], a 12.2% increase from the previous year and similar increases are evident in Scotland [14]. We have little understanding of how this growing NHS investment benefits patients, or if it can play a useful role in tackling an emerging public health problem. There is a need for clear, evidence-based guidance on the prescribing of high concentration fluoride toothpaste in older adults for caries prevention.

## Methods/design

### Trial aims and objectives

#### Aim

To evaluate the effectiveness and cost benefit of GDP prescribing of 5000 ppm fluoride toothpaste and usual care compared to with usual care alone in individuals 50 years and over with high-risk of caries.

Primary objectiveTo compare the effect of prescribing 5000 ppm fluoride toothpaste and usual care with usual care alone on treatment for caries, including coronal/root restorations, endodontics or extractionsTo compare the costs and benefits, within a net benefit framework of prescribing 5000 ppm fluoride toothpaste with usual care

Secondary objectives will evaluate the effect of prescribing 5000 ppm fluoride toothpaste on caries (mean Decayed Missing Filled Surfaces [DMFS]) increment, progression of early caries lesions, bleeding on probing, quality of life (generic and condition specific), costs to the NHS and to individuals and society, oral health behaviour and episodes of pain. In addition, we will explore the attitudes of clinicians and patients to the prescribing and use of high fluoride toothpaste.

### Study design

A two arm, parallel group, pragmatic, open label Randomised Controlled Trial (RCT) comparing the clinical effectiveness and cost benefit of GDP prescribed high concentration fluoride toothpaste and usual care compared to usual care alone in preventing and treating dental caries in older patients. The Medicines and Healthcare products Regulatory Agency (MHRA) has ruled that the trial should be categorised as a Type A trial, as described in Risk proportionate approaches in clinical trials [15].

A flow diagram for the trial is provided in Fig. 1. Follow up will last 3 years and will be conducted in multiple sites (approximately 60 General Dental Practices) located in England, Scotland and Northern Ireland.

**Fig. 1 Fig1:**
[figure not shown]
Trial Flow Diagram

In parallel with the trial we will undertake a qualitative project to understand GDPs’ practises and beliefs about prescribing 5000 ppm fluoride toothpaste and patients’ beliefs and experience of being prescribed 5000 ppm fluoride toothpaste and perceived impacts on their oral health related behaviours. Furthermore, this element will also provide GDPs’ and patients’ feedback concerning recruitment to inform our recruitment strategy. The qualitative protocol is included as Additional file 1: Appendix 1.

## Ethical considerations

Favourable ethical opinion for the REFLECT study was confirmed by the North East - Newcastle & North Tyneside 1 Research Ethics Committee on 17th November 2017 (REC reference number 17/NE/0329). The MHRA had no objection to the trial being classified as Type A under the notification scheme for risk-adapted Clinical Trials of Investigational Medicinal Products. The trial will be conducted according to the principles of Good Clinical Practice provided by Research Governance Guidelines [16]. Annual progress reports, notification of End of Trial, and a final report at the conclusion of the trial will be submitted to REC and to the MHRA within the timelines defined in the regulations. An independent Trial Steering Group supported by an independent Data Monitoring Group will oversee the conduct of the trial.

Participants are required to provide written informed consent to participate in the study, the consent form for the trial is included as Additional file 2: Appendix 2. Potential participants will receive a letter of invitation and a trial information sheet detailing the process and procedures of the trial and the nature of the intervention to be tested. Dentists will take informed consent using an approved consent form within the practices and will verbally reiterate the information contained in the information sheet and answer any questions that patients may have about the trial as part of the informed consent process. All participants will be given a £25 gift voucher at the start of the trial and another £25 voucher at the end in acknowledgment of the time that participation in the trial will entail and to thank them for their support. Consent from participants for direct access to data will also be obtained. The patients’ confidentiality will be maintained and will not be made publicly available to the extent permitted by the applicable laws and regulations.

## Study participants

Participants will be identified in multiple sites (approximately 60 General Dental Practices) located in England, Scotland and Northern Ireland. Participants will be NHS dental patients, 50 years of age or older who are considered by their dentist to be at high risk of developing caries. Our decision to use the lower limit of 50 years of age was based on: in the UK high concentration fluoride toothpaste is currently being prescribed to individuals between 50 and 60 years [17]; individuals 50 years and over have grown up in the absence of widespread use of fluoride toothpaste and consequently many individuals in this age group have heavily restored dentitions, increasing their caries risk [2]; the 2009 Adult Dental Health Survey suggests that those individuals with complex dental needs are most prevalent in late middle age [3]. Including a broad age range in the trial provides an opportunity to assess the impact of prescribing on different age groups in this older population.

High-risk individuals will be defined by: a diagnosis of active caries (into dentine) in the last 12 months which may/may not have been treated, or any root caries; and/or other risk factors as determined by their GDP. Participants can be living in any residential setting but must receive their dental care at a general dental practice (primary care). Participants will be assessed for inclusion by their GDP according to the trial inclusion and exclusion criteria.

***Inclusion criteria****:* People whoare aged 50 years or olderwith a diagnosis of active coronal caries (into dentine) in the last 12 months which may\may not have been treated, or any root caries; and\or other risk factors as determined by their GDP.receive their dental care in part or fully as an NHS patientare living in any residential setting, andfor whom their GDP decides prescription of high concentration fluoride toothpaste is appropriate for the patient

***Exclusion criteria:*** People who:are currently prescribed (by GDP or GP) high concentration fluoride toothpaste (for GDPs prescription must have been issued at last examination visit)hypersensitivity for Sodium Fluoride and\or other ingredients used in 5000 ppm toothpasteare living in the same household as someone already recruited to Reflect, or someone who is routinely using a high concentration fluoride toothpasteare unable to provide informed consent

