## Trial intervention

The trial intervention is prescription of 5000 ppm fluoride toothpaste, used as prescribed by the participant’s GDP and informed by national guidance [12]. The intervention is designed to reflect current dental practise and therefore the frequency of prescription, the number of tubes of toothpaste per prescription and the duration of the regimen will be determined by the patient’s GDPs after assessing each patient’s risk. We have restricted the intervention to 5000 ppm fluoride toothpaste, as NHS prescribing data shows that 5000 ppm is more commonly prescribed than the 2800 ppm alternative [17].

Current guidance recommends that for those adults with obvious *active* coronal or root caries dentists should prescribe high fluoride toothpaste [12]. Our inclusion criteria are less restrictive to allow for prescription based not just on caries activity, but also based on other risk factors, as determined by the GDP. This approach is based on the hypothesis that 5000 ppm fluoride toothpaste can prevent caries in those patients deemed to be high risk by their dentist, even though they don’t present with ‘obvious’ caries. For true primary prevention, the identification of risk factors in advance of disease is indicated.

The Investigational Medicinal Product (5000 ppm fluoride toothpaste) prescribed will not be specified by manufacturer or individual product. A clinical trials pharmacy will not be used to dispense the drug. The drug will be used as prescribed by the participant’s GDP and as indicated by the British National Formulary. Participants will be expected to collect their prescriptions at a local community pharmacy as per usual practice. GDPs will provide instructions to each participant based on their assessment of risk and how they prescribe the drug.

Compliance will depend on both GDPs’ and participants’ behaviour, the trial will not seek to ensure a minimal level of compliance. Compliance will be assessed to determine its impact on trial outcomes by recording GDPs’ self-reported prescribing behaviour frequency and duration of prescriptions and the number of tubes prescribed, accessing national datasets to identify if participants’ re-deem prescriptions or receive prescriptions from other sources and via participants’ (both test and control groups) self-reported use of toothpaste.

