The comparator will be usual care; usually advice given by the participant’s GDP to buy ‘standard’, off-the-shelf 1350-1500 ppm fluoride toothpaste and use as advised by their dentist informed by national guidance [12]. Other recommendations in the national guidance [12] for self-administered (mouthwash) or professionally-applied (varnish) fluoride delivery methods could have an impact on the trial. We will take a pragmatic approach and leave the decision to use other fluoride delivery systems to the patients and their dentist, but the use of these interventions will be recorded.

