## Follow up of participants

Participants will be followed up for a 3-year period. Participants will remain in the trial unless they choose to withdraw consent or if they are unable to continue for clinical reasons. All changes in status with the exception of complete withdrawal of consent will mean the participant is still followed up for all trial outcomes wherever possible. Participants randomised to 5000 ppm fluoride toothpaste, who for whatever reason, stop using the trial medication or participants randomised to routine care but who purchase or otherwise receive high fluoride toothpaste will not be considered to have withdrawn from the trial.

The Sponsor and CI have undertaken an initial risk assessment, which will be periodically reviewed and if necessary updated as the trial progresses. The Sponsor has concluded that this is a low risk trial, as the drug is being prescribed by GDPs as per its licensed indications. It is topically administered and the known side effects are rare and minor in nature [23].

Any Serious Adverse Reactions (SARs) will be recorded from the time a participant consents to join the study until the end of their follow up. The local investigator (GDP) will record in the CRF all directly observed Adverse Reactions (ARs) and all ARs spontaneously reported by participants that have a possible causal link to the IMP. In addition, each trial participant will be asked to complete a questionnaire at each attendance at their dental practice, and one sent annually to their home, which collects information on potential ARs and SARs.

The Sponsor and CI will ensure, through the independent Trial Steering Committee, that adequate systems are in place for monitoring the quality of the trial (compliance with appropriate governance) and appropriate expedited and routine reports, to a level appropriate to the risk assessment of the trial.

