## Sample size considerations

The sample size calculation is based on a meaningful absolute target difference of 10% (75% vs 65%) in the primary outcome measure. This difference is considered to be both a realistic and important difference from discussion with dentists, PPI groups and from published estimates [6, 7]. The value for the comparator group (75% of individuals allocated to standard care who have restoration(s) or extraction(s) due to caries during the 36 months of follow up) is based on published data and Scottish treatment data [24]. For the proposed target difference, a two-sided 5% significance level, and 90% power, 440 participants (880 in total) will be required to provide data for the primary outcome at 36 months. Based on our previous and current HTA trials, we are assuming 25% attrition, and so 587 participants per group are required (1174 in total) in approximately 60 practices (each practice recruiting an average of 20 participants). Based on an estimated consent rate of 50% [data from IQuad [25]], 2348 eligible patients will be invited to participate.

An important secondary outcome within our proposed trial is caries increment, measured using the number of Decayed Missing and Filled tooth Surfaces (DMFS). Using the mean number of Decayed Missing and Filled tooth Surfaces (DMFS), the caries increments for an older population in the published literature vary, but there seems to be consensus around one surface per year [26]. Given the fact that the standard deviations approximate the means in terms of caries increment, a reduction in caries increment from 3 to 2 surfaces with the intervention would produce a ~ 30% reduction in caries increment with the intervention over 3 years. The numbers needed to adequately power this secondary outcome are relatively small compared with the primary outcome measure:

For secondary caries outcomes (Scotland only), group sample sizes of 200 and 200 achieve 97.5% power to reject the null hypothesis of equal means when the population mean difference DMFS increment is μ1 - μ2 = 2–3 = − 1.0 with standard deviations of 2 for group 1 (intervention) and 3 for group 2 (control), and with a significance level (alpha) of 0.05 using a two-sided two-sample t-test allowing for unequal variances. Assuming 25% attrition, 267 participants per group are required (534) in total in 28 practices. Based on an estimated consent rate of 50% 1068 eligible patients will be invited to participate.

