## Statistical analysis

Statistical analysis will be conducted according to a detailed statistical analyses plan (SAP) which will include, but not be limited to the investigational plan and study design, listing of outcomes and final analysis including effectiveness evaluations. The SAP will set out the summary measures to be reported; methods of analysis, plans for handling missing data, non-compliance and withdrawals, the timing and frequency of analyses, and use of intention to treat analysis.

Demographic (age, sex) and baseline characteristics (DMFT, DMFS, concomitant illness / treatment, exempt\not exempt from NHS dental charges) will be summarised and displayed in tables for all randomised patients. In addition, mean NHS treatment costs in the 12 months prior to recruitment will be included in the baseline characteristics tables. Frequency counts and percentages will be used to present categorical data. Number of patients, mean, mode, median, SD, minimum, maximum and IQR will be used, as appropriate, to present continuous data.

The primary outcome measure will be analysed using a generalised linear model with the appropriate link function adjusting for the minimisation variables (recruitment site, residential setting, exemption (including partial exemption) from dental treatment charges and age band). Secondary outcomes will be analysed using generalised linear models with adjustment for minimisation and baseline variables when available. Statistical significance will be at the 2-sided 5% level with corresponding confidence intervals derived. Subgroup analyses on the primary outcome will explore the possible modification of treatment effect by clinically important factors; gender, age and NHS dental charges exemption status. This will be done by including treatment-by-factor interactions in the model and they will be classified as exploratory analyses. All analyses will initially be performed on an intention to treat basis, although we will consider additional analysis groups such as per-protocol for investigation of adverse events.

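### The exclusion of existing high-fluoride patients rests on a dental script from the last examination, not on the candidate's own use, so some current users can be randomised and could dilute the contrast

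*Protocol article*

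**What the plan says.** All references are to the protocol article.

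- **Study participants, exclusion criteria.** People are excluded who "are currently prescribed (by GDP or GP) high concentration fluoride toothpaste (for GDPs prescription must have been issued at last examination visit". The visit condition is attached to dental prescriptions only; a current prescription from a general medical practitioner excludes without it. A separate criterion in the same list excludes a person who lives with someone routinely using such a toothpaste.
- **Background.** The product is obtained on prescription, and its use is growing: "high concentration, prescription-only fluoride toothpaste has been used increasingly".
- **Trial intervention.** For the intervention arm, "the frequency of prescription, the number of tubes of toothpaste per prescription and the duration of the regimen will be determined by the patient’s GDPs". For the control arm, "The comparator will be usual care; usually advice given by the participant’s GDP to buy ‘standard’, off-the-shelf 1350-1500 ppm fluoride toothpaste". Use is to be recorded in both arms, including "via participants’ (both test and control groups) self-reported use of toothpaste".
- **Follow up of participants.** After allocation, "participants randomised to routine care but who purchase or otherwise receive high fluoride toothpaste will not be considered to have withdrawn from the trial".
- **Statistical analysis.** "All analyses will initially be performed on an intention to treat basis".
- **Sample size considerations.** The trial is sized on a "meaningful absolute target difference of 10% (75% vs 65%) in the primary outcome measure".

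**The concern.** The trial compares prescribing 5000 ppm toothpaste plus usual care with usual care alone. That contrast is cleanest when nobody is already using the product at entry. The exclusion is evidently meant to secure this, but for dental prescriptions it tests one administrative event, a script at the last examination, in place of exposure.

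Two kinds of current user pass the rule as written: someone still using tubes from a script issued before the last examination, and someone whose dentist wrote the script at a treatment or urgent visit. Neither is far-fetched. Every candidate must be a person for whom the dentist thinks the product appropriate. One route to eligibility is active caries in the past 12 months that may already have been treated, so visits other than examinations are foreseeable. The Background also reports rising prescribing.

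The household criterion shows that the authors regarded use as a workable ground for exclusion. A housemate's routine use disqualifies the candidate; the candidate's own use does not.

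If such people are randomised, some controls may have the exposure under test for part of follow-up. The primary analysis keeps them in their allocated arm, so any effect of this on the estimate is towards no difference.

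**Working it through.** **Step 1: what the rule lets through.** Applying the exclusion list as written to people using the product at entry:

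| Source of current use | Excluded as written? |
|---|---|
| Dental script at the last examination | Yes |
| Dental script at an earlier examination, tubes still in use | No |
| Dental script at a treatment or urgent visit | No |
| Current prescription from a general medical practitioner | Yes |
| Candidate does not use it but lives with a routine user | Yes |

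The gap is the second and third rows.

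**Step 2: reproduce the plan's sample size.** Inputs from Sample size considerations: p1 = 0.75, p2 = 0.65, two-sided 5%, 90% power. With pooled variance under the null and no continuity correction,

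n = [1.960 × √(2·p̄·(1−p̄)) + 1.282 × √(p1(1−p1) + p2(1−p2))]² / (p1−p2)²

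Here p̄ = 0.70, so the roots are √0.42 = 0.648 and √0.415 = 0.644. This gives (1.270 + 0.826)² / 0.01 ≈ 439.2, rounded up to 440 per group. Dividing by 0.75 for 25% attrition gives 587. Both match the plan. Power at 440 is 90.0%.

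**Step 3: illustrate dilution.** The documents give no share of existing users, so let f be an *assumed* share of controls who are existing users and keep the full 10-point benefit for all three years. The intervention rate stays at 0.65 and the control rate becomes 0.75 − 0.10f, so the difference is 0.10(1 − f). Power is

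Φ{ [d√440 − 1.960√(2p̄(1−p̄))] / √(p1(1−p1) + p2(1−p2)) }, where d is the diluted difference.

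For f = 10%: p1 = 0.74, d = 0.09, p̄ = 0.695. The numerator is 0.09 × 20.976 − 1.960 × 0.651 = 1.888 − 1.276 = 0.612, the denominator is √0.4199 = 0.648, and the ratio is 0.944, giving Φ = 0.827.

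| Assumed f | Control rate | Difference | Power at 440 per group |
|---|---|---|---|
| 0 | 75.0% | 10.0 points | 90.0% |
| 2% | 74.8% | 9.8 points | 88.8% |
| 5% | 74.5% | 9.5 points | 86.7% |
| 10% | 74.0% | 9.0 points | 82.7% |
| 20% | 73.0% | 8.0 points | 72.8% |

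Power goes below 80% once f exceeds about 13%.

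**Step 4: what the table means.** For a given f these are the largest losses. A control whose supply ends keeps only part of the benefit, so the true difference would lie between the tabulated one and 10 points.

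**The case against.** The strongest reply is that prescription is the intervention. The trial tests a prescribing policy in ordinary practice, so excluding by prescription fits the question, and tying the word current to the last examination makes the rule checkable from the practice's own records. The household rule may rest on use only because the practice may hold no record for a housemate. These are fair reasons for having a prescription test. They do not explain why a candidate known to be using the product should enter: for that person, allocation tests renewing supply, not starting it.

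Other parts of the reply stand and limit the point.

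- A reader might infer that existing users will carry on through follow-up in the control arm. The documents do not say so. Someone with no script at the last examination has only leftover tubes unless a new source appears, and no tube life, number of tubes per script or examination interval is given.
- A reader might cite the sentence on controls who obtain the product. It concerns crossover after randomisation, which no entry criterion would remove; it is not evidence of use at entry.
- A reader might infer that existing users contribute nothing to the comparison. That is too strong: a prior user in the intervention arm can be prescribed the product for three years, while one in the control arm may run out.
- The target difference is described as realistic, and it is not stated whether it already allows for some crossover.
- Prescribing, redemption and self-reported use are recorded in both arms, and handling of non-compliance is left to an SAP that is not shown. The lack of a stated sensitivity analysis in the article is therefore not a fault.

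**Conclusion.** The point holds as a gap in the eligibility wording, and as a mismatch with the use-based household rule. Some people already using the product through dental scripts issued outside the last examination can be randomised, and nothing in the text stops them from continuing in the control arm.

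The likely direction is dilution. Its size cannot be established, because the share of existing users and the duration of their continued use are not given. The figures of 87%, 83% and 73% depend on assumed shares of 5%, 10% and 20%, on full benefit for three years, and on a 10-point target that makes no allowance for crossover. The documents do not support concluding that the trial is underpowered; the stated sample size reproduces exactly. This is a cheap improvement worth making, not a flaw that undermines the primary comparison.

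**What to change.** Keep the prescription criterion and add one line beside it: exclude people who are currently using high-concentration fluoride toothpaste from any source. Check it with the baseline self-report of toothpaste use, completed before randomisation. Outcome measures and Table 1 already list oral health behaviour at baseline; the trial team should confirm that the item distinguishes high-concentration toothpaste. The article reports recruitment as still open, so the change could apply to remaining recruits.

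For participants already randomised, identify current users from baseline data only, and add a sensitivity analysis of the primary outcome without them, if the SAP does not already contain one. Selecting on information fixed before allocation keeps the remaining comparison randomised; use recorded during follow-up should not be used for this purpose. Reporting the number of baseline users by arm would also replace the assumed share above with an observed one.

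The cost is an amendment of one line, one extra analysis on data already planned for collection, and a slightly smaller eligible pool.
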